# QUality improvement in primary care to prevent hospitalisations and improve Effectiveness and efficiency of care for people Living with coronary heart disease (QUEL): protocol for a 24-month cluster randomised controlled trial in primary care

**DOI:** 10.1186/s12875-020-01105-0

**Published:** 2020-02-14

**Keywords:** Quality improvement, Primary care, Secondary prevention, Coronary heart disease, Data, Cardiovascular disease, Health services, Data linkage

## Abstract

**Background:**

Cardiovascular disease (CVD), including coronary heart disease (CHD) and stroke, is the leading cause of death and disability globally. A large proportion of mortality occurs in people with prior CHD and effective and scalable strategies are needed to prevent associated deaths and hospitalisations. The aim of this study is to determine if a practice-level collaborative quality improvement program, focused on patients with CHD, reduces the rate of unplanned CVD hospitalisations and major adverse cardiovascular events, and increases the proportion of patients achieving risk factor targets at 24 months.

**Methods:**

Cluster randomised controlled trial (cRCT) to evaluate the effectiveness of a primary care quality improvement program in 50 primary care practices (n~ 10,000 patients) with 24-month follow-up. Eligible practices will be randomised (1:1) to participate in either the intervention (collaborative quality improvement program) or control (standard care) regimens. Outcomes will be assessed based on randomised allocation, according to intention-to-treat. The primary outcome is the proportion of patients with unplanned CVD hospitalisations at 2 years. Secondary outcomes are proportion of patients with major adverse cardiovascular events, proportion of patients who received prescriptions for guideline-recommended medicines, proportion of patients achieving national risk factor targets and proportion with a chronic disease management plan or review. Differences in the proportion of patients who are hospitalised (as well as binary secondary outcomes) will be analysed using log-binomial regression or robust Poisson regression, if necessary.

**Discussion:**

Despite extensive research with surrogate outcomes, to the authors’ knowledge, this is the first randomised controlled trial to evaluate the effectiveness of a data-driven collaborative quality improvement intervention on hospitalisations, CVD events and cardiovascular risk amongst patients with CHD in the primary care setting. The use of data linkage for collection of outcomes will enable evaluation of this potentially efficient strategy for improving management of risk and outcomes for people with heart disease.

**Trial registration:**

Australian New Zealand Clinical Trials Registry (ANZCTR) number ACTRN12619001790134 (dated 20th December 2019).

## Background

Cardiovascular disease (CVD), including coronary heart disease (CHD) and stroke, is the leading cause of death and disease burden globally [1]. CHD accounts for the greatest single disease morbidity and nearly one fifth of all deaths, with around a third of these occurring in people who have prior CHD [2, 3]. With an aging population, and more people surviving initial events, the burden of CHD is increasing and is projected to rise from around 47 million disability-adjusted life years (DALYs) globally in 1990 to 82 million DALYs by 2020 [3]. However, despite international guidelines recommending secondary prevention [4–6], adherence, access and sustainability of their implementation is suboptimal. Use of evidence-based secondary prevention medications and lifestyle change both decline in the initial 6 months after an event [7] and continue to decline thereafter [8]. Therefore, improving post-discharge care through secondary prevention strategies (healthy living, adherence to medicines) is an international priority requiring innovative and efficient strategies that support better patient care [9, 10].

Collaborative quality improvement initiatives offer an efficient way to support and improve health service delivery on a large scale. These ‘purposeful efforts to secure positive change’ have become a focus of activity within the international healthcare environment [11]. In response to increasing health demand, the Institute for Healthcare Improvement (US) developed the Breakthrough Collaborative Quality Improvement Methodology to make rapid improvements in quality while reducing costs [12]. This approach offers a scalable model by targeting stakeholders to drive improvement, leveraging the collective power of sites working simultaneously on the same problem and using data to drive performance [12]. Collaborative methodology has been applied to a range of healthcare systems with demonstrated success in areas such as asthma [13], chronic heart failure [14] and compliance with healthcare standards [15, 16]. While such programs have been evaluated, evidence for their impact and effectiveness has only focussed on surrogate endpoints and more robust evidence is needed [17, 18].

In recent years, the expansion of technology has enabled the integration of automated data extraction, which has expanded opportunity for data-driven quality improvement [19]. For example, in primary care, practices can utilise their routinely collected data to inform practice-level decision-making and implementation of associated quality improvement [20]. As such, a focus on data-driven quality improvement has become a key element within contemporary literature outlining the building blocks of high performing primary care practices [21]. Current data shows that only 38% of Australian patients with CVD receive a government-funded chronic disease management plan from their primary care provider [22]. The aim of the QUEL (QUality improvement in primary care to prevent hospitalisations and improve Effectiveness and efficiency of care for people Living with CHD) study is to evaluate whether a data-driven quality improvement program implemented in primary care reduces CVD hospitalisations and improves CVD risk factors and medication adherence in patients with CHD over 24 months.

Specific objectives are to determine if a primary care practice-level, collaborative quality improvement program:
i.reduces the rate of unplanned CVD hospitalisations and major adverse cardiovascular events (MACE) at 24 months in patients with CHD;ii.increases the proportion of patients who are prescribed evidence-based medications for CVD, are achieving national targets for risk factors (cholesterol, blood pressure (BP), smoking) and have an active Chronic Disease Management (CDM) or review plan in place and to;iii.determine barriers and enablers associated with implementation of the quality improvement program.

## Methods/design

### Study design

QUEL is a cluster randomised controlled trial (cRCT) with 1:1 randomisation recruiting 50 Australian primary care practices (n~ 10,000 patients with CHD) with 24-month follow-up to compare outcomes amongst practices allocated to collaborative quality improvement program versus standard care (Fig. 1). Data will be collected via linkage of routinely collected primary care practice data with administrative data (hospitalisations, deaths and pharmaceutical prescriptions).

**Fig. 1 Fig1:**
[figure not shown]
Flow diagram of QUEL cRCT

### Practices and patients

Primary care practices will be identified through Australian Primary Health Networks (PHNs) across two states of Australia (New South Wales, Queensland). Research team members and representatives from the Improvement Foundation (an Australian not-for-profit organisation providing consultancy and training services in quality improvement) will approach all PHNs in participating states and provide information about the study. Supportive PHNs will then communicate with primary care practices in their jurisdictions to seek expressions of interest (EOI) for participating. Research team members will coordinate receipt of EOIs and contact practice staff to confirm eligibility and commence formal recruitment processes, signing of agreements and enabling automated data extraction from practice software. Inclusion and exclusion criteria for practice are detailed below.

Practices will be eligible to participate if they;
i.manage ≥100 patients year with prevalent CHD andii.use practice software that is compliant with Improvement Foundation systems (such as Medical Director, Best Practice, Communicare, Monet and Clarity which account for the majority of practice management software market-share in Australia).

Practices will be excluded if:
i.they are unwilling to provide written agreement to participate in the quality improvement program orii.the primary care practice is already participating in a formal quality improvement project targeting CVD.

The patient cohort for the QUEL will comprise a dataset of all eligible patients presenting to participating practices who meet the following inclusion criteria.:
i.are ≥18 years with a documented diagnosis of CHD in the primary care record of a participating practice, andii.have visited the participating practice at least once in the previous 12 months.

### Ethics

This study will adhere to the National Health and Medical Research Council (NHMRC) ethical guidelines for human research [23] and processes are detailed elsewhere [24]. Given this is a cRCT with a practice-level intervention, patient data will be extracted with a waiver of consent. Ethics approval has been obtained from the New South Wales Population & Health Services Research Ethics Committee (HREC, HREC/18/CIPHS/44), which also meets the formal approval requirements for Queensland. A waiver of consent is required because it will be impractical to collect individual consent from each patient and data linkage will be via data extraction from clinical software. The intervention will occur at the practice-level and it is not anticipated there will be any harm to individual patients. However, if a practice wishes to withdraw from the study they will be free to do so at any time. Any necessary protocol amendments will be approved by the ethics committee, investigators, trial registries and if required the journal should the need arise.

### Intervention and control groups

Practices allocated to the intervention will participate in a CHD secondary prevention collaborative quality improvement program. The program is designed to use data and practice level engagement to implement rapid and progressive changes based on Plan, Do, Study, Act (PDSA) cycles for pre-determined performance targets [21]. The program is underpinned by the psychology of behaviour change, active practice-level engagement combined with extraction and utilisation of electronically extracted data from practice software [12]. Practices will collaborate and support each other between and within practices in an ongoing way over 12 months to achieve a set of key performance measures (Table 1). These measures have been pre-determined based on guidelines [6] and availability of data for extraction and were developed and approved through an iterative process involving study investigators, clinicians and quality improvement experts. Intervention practices will receive their summarised performance data monthly.

**Table 1 Tab1:** QUEL intervention key performance measures

• Proportion of patients with CHD where LDL has been recorded within the previous 12 months	
• Proportion of patients with CHD whose most recent LDL result was less than 2.0 mmol/L	
• Proportion of patients with CHD with a recorded BP reading taken within the previous 12 months	
• Proportion of patients with CHD whose most recent BP reading, taken within the previous 12 months, was less than or equal to 130/80 mmHg	
• Proportion of patients with CHD whose smoking status has been recorded	
• Proportion of patients with CHD recorded as a current smoker	
• Proportion of patients with CHD who are currently prescribed an anti-platelet agent	
• Proportion of patients with CHD who are currently prescribed a statin	
• Proportion of patients with CHD who are currently prescribed an ACE inhibitor or ARB	
• The proportion of patients with CHD with MBS Items 721 or 732 claimed (GP Management Plans or review)	
• Proportion of patients with CHD who have an influenza vaccination recorded within the previous 12 months	

*CHD* Coronary heart disease, *LDL* Low density lipoprotein, *BP* Blood pressure, Angiotensin-converting-enzyme (ACE) inhibitor, *ARB* Angiotensin II receptor blockers, *MBS* Medicare Benefits Scheme, *GP* General practice

The 12 month intervention will deliver the collaborative quality improvement program via (i) *Learning workshops* where a minimum of two practice staff (ideally one GP and one practice staff) participate in two online and two face-to-face learning workshops (based on Langley and Nolan model for improvement) [21]; (ii) *Activity periods* where practices use their own electronically extracted data to test and implement improvements through cycles of small step-wise changes; (iii) *Data reporting and feedback* where practices submit monthly data and PDSA cycles on which they are provided objective feedback (telephone and in-person visits) on their outcomes and progress and; (iv) *Transfer* where PHNs share learnings from practices within their jurisdictions [18]. Only personnel trained in delivery of collaborative quality improvement will deliver the practice support and all practices will have access to an online Sharepoint website for regular communication and support.

Practices allocated to the control group will participate in usual care without access to the quality improvement intervention for CHD during the study period. Control practices will be offered an opportunity to participate in a series of virtual workshops after data collection has closed. No individuals presenting to a participating practice (intervention or control) during the study period will be restricted in any way in terms of the care and treatment they receive from their healthcare providers. As this is a cRCT, it is not anticipated any post-trial care will be required for individual patients. However, after completion of follow-up, practices allocated to the control group will be offered the opportunity to receive support for quality improvement activities via a virtual program delivered by the Improvement Foundation. Their participation will be voluntary and will not impact on data collection.

### Outcomes

The primary outcome is the proportion of patients with unplanned CVD hospitalisations within 2 years of baseline data extraction (and commencement of intervention for those allocated to intervention group). For this study, CVD is defined as any condition involving the heart, brain or peripheral blood vessels and includes CHD (such as angina and myocardial infarction, MI), cerebrovascular disease (such as stroke), peripheral arterial disease and other conditions including heart failure and atrial fibrillation [25].

Secondary outcomes, also at 2 years) are;
i.Proportion of patients with major adverse cardiac and cerebrovascular events (fatal and non-fatal) that includes CHD (angina or MI), stroke or CVD death,ii.proportion of patients who received guideline-recommended medicines,iii.proportion of patients with a chronic disease management plan or review (Australian Medicare Item numbers 721 or 732 respectively) and;iv.proportion of patients achieving national targets for CVD risk factors (total cholesterol, systolic blood pressure, smoking).

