### Data collection and management

All data will be collected at baseline, 12 and 24 months. CVD hospitalisations and cardiovascular events will be collected via state-based administrative admissions data (depending on location of recruited practices). Individual patient deaths will be collected via linkage with the National Death Index and medication prescriptions and health service utilisation via linkage with the Australian Government Department of Health Pharmaceutical Benefits Scheme (PBS) and Medical Benefits Scheme (MBS) schemes respectively. Probabilistic matching will be used to link records and the estimated proportion of invalid and missed links using data linkage will be very low [26]. Data collection pertaining to the proportion of patients with chronic disease management plans and achieving national risk factor targets (cholesterol, smoking, and BP) will be electronically extracted from participating practice software systems using an automated data extraction tool with encrypted identifiers attached to patient data.

All data will be stored on a password-protected Secure Unified Research Environment (SURE), which is a purpose-built, remote-access data storage facility. This environment allows researchers to safely access, store and analyse study data [27]. Only aggregated and analysed data can be exported and data in SURE cannot be copied, downloaded or transmitted by email or other means. Only trained study research staff will have access to the SURE facility through a staff-specific username and password. The linked dataset will therefore be anonymised and the research team who will be analysing the data and delivering the intervention will not have access to individual-level data. This maximises privacy and forms an important aspect of the requirements for waiver of consent approval. Electronic files containing linked data for analysis will be stored on a Virtual Project Workspace within SURE and the access period shall be from study commencement for 7 years to enable all analyses to be completed. At the end of this data retention period, the tapes holding the archived data files will be physically destroyed.

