### Sample size

The target sample size is 6050 (3025 per group), obtained from 50 practices (25 per randomised group) with an average cluster size of 121 patients per practice. This is estimated to provide 80% power to detect a ratio of the group proportions (or relative risk) of 0.75. This sample size assumes a control group readmission rate of 35% based on a recent Australian cohort study (*n* = 6172) reporting an atherothrombotic disease readmission rate of 35% at 2 years for patients with CHD [28]. The estimation assumes a significance level of 0.05 and an intra-class correlation coefficient (ICC) of 0.05. The ICC is based on data from two cross-sectional studies in Australian primary care [29, 30]. Loss to follow-up is anticipated to be very minimal given the primary outcome will be obtained via data linkage [26].

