### Statistical analyses

Analyses will be conducted at the individual level while accounting for clustering of patients within practices. Intention-to-treat principle will be followed with patients analysed according to their randomisation group. Differences in the proportion of patients who are hospitalised (as well as binary secondary outcomes) will be analysed using log-binomial regression or robust Poisson regression in case of convergence issues. Clustering will be accounted for by modelling the correlation among patients from the same cluster using generalised estimating equations with an exchangeable correlation structure. Sensitivity analyses will include analyses of yearly rates using Poisson regression and/or time-to-event analyses via Cox models. Adjusted analyses will also be performed to account for baseline imbalances in cluster and patient characteristics. Pre-specified sub-group analyses will be used to determine the impact of the intervention on different patient groups (male v female; low SES v high SES, different CVD subgroups, influenza vaccination or not) and practice types (e.g., large v small and urban v rural). This will be done by adding the subgroup variable as well as its interaction with the intervention to the main analysis model. As data will be extracted from primary care practice clinical records and administrative data, if not recorded, it will be assumed that the task has not been done. A detailed analysis plan including mock tables will be developed and signed-off prior to unblinding.

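### The smoking target is compared across all CHD patients without using baseline smoking status, so an effect on quitting is diluted and lost in between-practice noise

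*Protocol article*

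**What the plan says.** Under Outcomes, the fourth secondary outcome at 2 years is the "proportion of patients achieving national targets for CVD risk factors (total cholesterol, systolic blood pressure, smoking"). The denominator is not restricted. Under Practices and patients, "The patient cohort for the QUEL will comprise a dataset of all eligible patients presenting to participating practices" who are adults with documented CHD and a visit in the previous 12 months, whether they smoke or not. Table 1 of the intervention section uses the same base: "Proportion of patients with CHD recorded as a current smoker". It also makes recording a programme measure: "Proportion of patients with CHD whose smoking status has been recorded".

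Under Statistical analyses, "Differences in the proportion of patients who are hospitalised (as well as binary secondary outcomes) will be analysed using log-binomial regression" (robust Poisson if that fails to converge), with GEE and an exchangeable correlation. No baseline covariate is named for this model. The section separately promises adjusted analyses for baseline imbalances in cluster and patient characteristics, without naming smoking. It also says that items not recorded will be taken as not done.

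Under Data collection and management, "All data will be collected at baseline, 12 and 24 months", so baseline smoking status is already in the extraction plan. Sample size covers the primary outcome only.

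**The concern.** A never-smoker or established ex-smoker with a recorded status is at target on day one. The programme can keep such a patient at target but cannot move them to it. If most of the cohort is in that position, even a large change in quitting moves the all-patient proportion by a point or two, and the ratio stays close to 1. An unadjusted comparison of 25 with 25 practices also carries the whole spread in smoking prevalence between practices, which has nothing to do with the programme.

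The smoking part of objective ii is at stake. A useful effect on quitting could be reported as no effect, a chance difference in baseline prevalence could obscure or mimic one, and the reported relative risk could not be read as a change in quitting. The baseline information that would prevent most of this is already collected.

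**Working it through.** **Inputs from the protocol (Sample size).** "The target sample size is 6050 (3025 per group), obtained from 50 practices (25 per randomised group"). Mean practice size 121, ICC 0.05, significance level 0.05 (taken as two-sided), control rate 35% and relative risk 0.75 for the primary outcome.

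**Assumed, not in the protocol.** Baseline smokers s = 10%, 15% or 20%; control quit rate q = 5% to 20%, doubled by the programme; ICC 0.05 applied to smoking; complete recording; no relapse.

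**The protocol's own figure.** Design effect 1 + (121 − 1) × 0.05 = 7. Per arm, unclustered: 7.849 × (0.35 × 0.65 + 0.2625 × 0.7375) / 0.0875² = 432. Then 432 × 7 × 2 = 6048, against 6050 stated. It reproduces, so 3025 / 7 = 432 is the effective number per arm used below.

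**All-patient outcome, unadjusted.** Control proportion at target = 1 − s(1 − q); intervention = 1 − s(1 − 2q). For s = 15%, q = 10%:
- 1 − 0.15 × 0.90 = 86.5%; 1 − 0.15 × 0.80 = 88.0%; ratio 1.017.
- SE = √[(0.865 × 0.135 + 0.88 × 0.12) / 432] = 0.0227.
- Power = Φ(0.015 / 0.0227 − 1.96) = Φ(−1.30) = 9.7%.

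**Among baseline smokers.** For s = 15% there are 0.15 × 121 = 18.15 per practice, about 454 per arm. Design effect 1 + 17.15 × 0.05 = 1.86, effective n = 244. SE = √[(0.09 + 0.16) / 244] = 0.0320. Power = Φ(0.10 / 0.0320 − 1.96) = Φ(1.17) = 88%.

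| s (quitting 10% v 20%) | At target, control v intervention | RR | Power, all patients | Power, baseline smokers |
|---|---|---|---|---|
| 10% | 91.0% v 92.0% | 1.011 | 8% | 79% |
| 15% | 86.5% v 88.0% | 1.017 | 10% | 87–88% |
| 20% | 82.0% v 84.0% | 1.024 | 12% | 91% |

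**Simulation of the same scenarios** (practice-level smoking and quit probabilities from beta distributions with ICC 0.05). It allows for unequal numbers of smokers per practice and 50 clusters:
- All patients, unadjusted: about 9% to 13%.
- All patients, adjusted only for the practice's baseline smoking proportion: about 66% to 84%, type I error about 3% to 4%.
- Baseline smokers only: about 72% to 86% (88% at the top in some runs).

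The adjusted figure comes from a linear model of practice proportions with robust errors, not from the protocol's GEE, so it indicates the gain rather than fixing it.

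**Sensitivity of the unadjusted all-patient power** (normal approximation, s = 10% to 20%, counting only significant results in the programme's favour):
- q = 5%: 4% to 6%, RR 1.006 to 1.012.
- q = 15%: 13% to 23%, RR 1.016 to 1.036.
- q = 20%: 21% to 40%, RR 1.022 to 1.048.
- q = 10%, ICC 0.01: 15% to 29%.
- q = 10%, 10,000 patients (200 per practice), ICC 0.05: 8% to 12%.

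**Recording.** Suppose unrecorded status counts as not at target, s = 15% and q = 10% in both arms, and recording is an assumed 80% in control and 90% in intervention. The proportions are 0.80 × 0.865 = 69.2% and 0.90 × 0.865 = 77.9%, a ratio of 1.125 with about 82% power and no change in quitting.

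**The case against.** The strongest reply is that the denominator is not the main cause of the low power. With every patient kept in, adjusting for baseline smoking recovers most of it. The protocol already plans adjusted analyses, and covariate lists usually belong in a SAP, which is not shown. This stands in large part, and it is why the all-patient outcome should stay. Two things remain. The adjusted analyses are additional to the main model and are aimed at imbalance, and smoking is not named. Adjustment also restores precision, not interpretability: the all-patient ratio stays near 1 and still does not describe quitting.

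A second reply is that objective ii asks about the proportion of patients achieving targets, and a whole-practice denominator suits a practice-level programme. That stands. A reader might infer that the denominator is wrong and should give way to quitting among smokers, but that would replace the trial's stated question.

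A reader might also infer that only baseline smokers can move to target. The document does not support that. If the rule on unrecorded items applies to smoking, a non-smoker with no recorded status counts as not at target and can move to it once recorded.

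Finally, this is one component of one secondary outcome and the protocol claims no power for it. That is correct.

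**Conclusion.** The concern holds in a limited form. The smoking component is fixed on all CHD patients and its main model, as described, ignores baseline smoking status. That choice dilutes an effect on quitting and adds avoidable noise.

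The dilution towards 1 follows from the definition and does not depend on the ICC. The power figures do depend on assumptions. About 9% to 13% applies to ICC 0.05, 10% to 20% baseline smokers, quitting of 10% v 20% and complete recording. Over the wider range at ICC 0.05 it is about 4% to 40%. A reader might take 10% as the trial's power for smoking; the protocol supplies neither prevalence, quit rate nor a smoking ICC, so it is one slice of that range. Nor is any stated figure contradicted, because only the primary outcome is powered. The point is worth acting on because the gain is large in the ICC 0.05, 10% v 20% scenarios and needs no new data.

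**What to change.** Before unblinding, in the outcome definition and the analysis plan:

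1. Keep the all-patient proportion at the smoking target at 24 months as the outcome that answers objective ii, and put baseline smoking (patient status or practice proportion) in its main model.
2. Add as a pre-specified formal analysis, with the same GEE model, the proportion of patients recorded as current smokers at the baseline extraction who are recorded as non-smokers at 24 months.

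Leave the cholesterol and blood pressure components as they are. Quote any power for smoking as a range under stated assumptions.

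The cost is wording only. The downsides are a smaller denominator in the second analysis, limited to patients with smoking status recorded at baseline, and relapse among ex-smokers appearing only in the all-patient outcome. Neither analysis removes dependence on how well practices record and update smoking status at 24 months, which the programme itself targets, so results should be read beside the proportion recorded in each arm.
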